## **9. ETHICAL CONSIDERATIONS**

### **9.1 Regulation statement**

The trial will be conducted according to the Medical Research Involving Human Subjects Act (WMO) and adheres to the ethical principles that have their origin in the declaration of Helsinki.

Patient privacy is ensured by de-identifying all submitted data and using a subject identification code. All patients will have the right to withdraw from the study at any time during the trial.

### **9.2 Recruitment and consent**

When patients are found eligible for re-irradiation by a multidisciplinary neuro-oncology tumor board, they will be asked by the treating physician if they are willing to be informed on the study. Subsequently, study information will be provided to the patient. Prior to radiotherapy preparations, that will be typically some days later, patients will be asked for consent by the BROK-certified researcher or physician and if the patient is willing to participate, after the informed consent procedure the baseline characteristics will be collected.

### **9.3 Benefits and risks assessment, group relatedness**

Aside from a reduced number of hospital visits for the intervention group, no individual benefits and no known risks are associated with participation in this trial. The radiation doses that will be administered have already proven to be safe in previous studies[26, 35]. To reduce patients' burden hospital visits are limited to standard follow-up. Most additional follow-up assessments will be performed by phone call or by self-administered forms. We choose to use the EQ-5D-5L at time points 2, 4 and 6 weeks and thereafter the QLQ-C15-PAL instead of the QLQ-C30 to assess HRQoL. The questionnaires can be completed in less than 10 minutes at home. Additionally, during a phone call of a few minutes patients will be asked about AEs, anti-edema treatment and reminded to complete their HRQoL assessments.

### **9.4 Compensation for injury**

The sponsor has a liability insurance which is in accordance with article 7 of the WMO.

The sponsor also has an insurance which is in accordance with the legal requirements in the Netherlands (Article 7 WMO). This insurance provides cover for damage to research subjects through injury or death caused by the study.

The insurance applies to the damage that becomes apparent during the study or within 4 years after the end of the study.

### **9.5 Incentives**

When the visits are not included in the standard follow-up, travel and parking cost will be reimbursed.

## **10. ADMINISTRATIVE ASPECTS, MONITORING AND PUBLICATION**

### **10.1 Handling and storage of data and documents**

The handling of personal data will comply with the General Data Protection Regulation (GDPR) (In Dutch: Algemene Verordening Gegevensbescherming (AVG)), so data will be handled confidentially and coded.

#### **10.1.1 Data Collection**

Study sites will register a patient in the web-based application Ldot after informed consent of the patient. Each user will get a personal account to allow access to his/her own studies, site(s), subjects and specific viewing rights. After registration of the patient, Ldot will generate a unique study registration (USR) number. Access to Ldot can be granted by different roles. A “role based” access to the system will avoid unauthorized data access and prevents users to perform action they are not allowed to do.

Users have access to the system using their personal username and password plus 2FA/SRAM (SURF Research Access Management). The system uses an electronic audit trail to log changes of important variables with timestamps and user information. Ldot data traffic over the internet is encrypted using secured data communication protocols.

Databases and web servers of Ldot application are hosted in data centers that meets the highest available standards for security. Access to the ICTS server rooms is limited by physical and automatic access security, and is supported by fire protection and continuity guarantees in the field of energy supply. The ICTS servers are protected by firewalls and measures have been taken to support random irregularities on the network. The servers are placed in a specially secured VLAN. Data guarantee has been established for each ICT system: the data is regularly backed up and regularly tested to see whether this backup can be restored.

The observational data will prospectively be collected from medical charts, pathology reports, radiology reports, neurocognitive function tests and web-based surveys (PROFILES web-based database). The interfaces will be realized using common, standard and secure software.

Data collected through web-based surveys will be sent to the central RISinG database coded without patient identifiers. Enrolled participants will be assigned study identification codes that will not resemble medical record number, governmental identification or other unique identifiers. Participants who are not able to use the web-based surveys will be offered hardcopy questionnaires instead. Hardcopy questionnaires will be entered in the PROFILES web-based database after secured login. The hardcopy questionnaires will then be physically stored in a secure archive of the UMC Utrecht.

In addition to the pseudonymized clinical data, technical data on imaging and radiation plans will be collected as well. These will be stored in the Research Imaging Architecture (RIA), a

fully secure data storage infrastructure. This storage infrastructure runs tools to manage incoming and outgoing data, verifies the origin (approval) of incoming data requests and several other logistics. These represent a dynamic adaptable toolset (which exists on both entities) that can be used to perform various activities on technical patient data before it is sent or just as it is being received. Example activities include: de-identifying, pseudonymizing and/or anonymizing data, packaging/deflating incoming data using encryption key, verifying (point-to-point) communication, handling incoming duplicated data according to rule set and retrying logic (robustness) in case of network issues or maintenance.

All data will be analyzed by the investigators of this study and the data will be kept for at least 15 years.

#### **10.1.2 Safeguard of key to code**

A separate identification log only containing codes with corresponding patient identifiers (name, date of birth, sex and date of inclusion), will be stored on a different secured location within the UMCU to prevent the possibility to directly match study data with patient identifiers. The same manner of coding will be used for all studies within the RISinG project. The participant's name and personal data will remain confidential and will not be published in any way, however, the sponsor's monitor or representative and regulatory representatives (FDA and/or European Communities EU Notified Body Representatives), auditors and inspectors may have access to medical files in order to verify authenticity of data collected.

In order to send questionnaires, patient identifiers (name, date of birth, sex and address) necessary to send questionnaires will be stored in the PROFILES web-based database which is accessible after secured login. Employees of PROFILES could have access to these patient identifiers as well. PROFILES is part of the Dutch Cancer Registry (in Dutch: Integraal Kankercentrum Nederland, IKNL) and complies with the General Data Protection Regulation, so data will be handled confidentially and coded. Upon informed consent patients are aware that their patient identifiers will be used by employees of PROFILES in order to send questionnaires.

#### **10.1.3 Data extraction**

Requested data can be extracted from the RISinG database by exporting data to Excel, SPSS and/or R. Data will only be exported coded (i.e. without any identifying information such as patient name, initials, social security number).

#### **10.1.4 Data sharing with participating hospitals**

Upon informed consent patients are aware that their pseudonymized data may be shared with participating hospitals in favor of conducting the research described in this application. These data will remain property of this project and will only be provided upon request and after quality check at/by the research board of this project.

### **10.2 Monitoring and Quality Assurance**

The monitoring of the study will be performed by a qualified and trained monitor to assure the quality and validity of the research data. The monitoring will be performed according to the NFU (Nederlandse Federatie van Universitaire Medische Centra) guidelines. The monitoring plan is included in the application.

### **10.3 Amendments**

Amendments are changes made to the research after a favorable opinion by the accredited METC has been given. All amendments will be notified to the METC that gave a favorable opinion. Non-substantial amendments will not be notified to the accredited METC and the competent authority, but will be recorded and filed by the sponsor.

### **10.4 Annual progress report**

The sponsor will submit a summary of the progress of the trial to the accredited METC once a year. Information will be provided on the date of inclusion of the first subject, numbers of subjects included and numbers of subjects that have completed the trial, serious adverse events/ serious adverse reactions, other problems, and amendments.

### **10.5 Temporary halt and (prematurely) end of study report**

The investigator/sponsor will notify the accredited METC of the end of the study within a period of 8 weeks. The end of the study is defined as the last patient's last visit.

The sponsor will notify the METC immediately of a temporary halt of the study, including the reason of such an action.

In case the study is ended prematurely, the sponsor will notify the accredited METC within 15 days, including the reasons for the premature termination.

Within one year after the end of the study, the investigator/sponsor will submit a final study report with the results of the study, including any publications/abstracts of the study, to the accredited METC.

### **10.6 Public disclosure and publication policy**

Results will be published with open access unreservedly regardless of their nature in accordance with the CCMO statement on publication policy. The current PhD-student will be first author and the PI last author. Every center that includes patients, added to this protocol in amendments, will be provided authorship.

## Appendix

### 1. Radiotherapy Treatment Protocol for arm 1

#### 1.1 Equipment and Planning

Radiotherapy will be planned and delivered with modern techniques including at least intensity modulated radiation therapy (IMRT) and volumetric modulated arc therapy (VMAT).

#### 1.2 Immobilization

All participants will be immobilized in a customized thermoplastic shell or relocatable stereotactic frame in a supine position according to institutional standards.

#### 1.3 Data acquisition and Definitions of Target Volumes and Organs at Risk

The definition of volumes will be in accordance with the International Commission on Radiation Units and Measurements (ICRU) Report 50, ICRU Report 62. Volumes will be defined based on a volume MRI scan with contrast (T1+Gadolinium, CE-T1) and co-registered to a computerized tomography (CT) scan. The MRI scans must have a maximum 2 mm and isotropic voxels, the CT should have 1-3mm slice thickness. Amino-Acid-PET or SPECT-Examinations may be used in addition to contrast-enhancement on MRI for target volume definition but are not mandatory.

##### 1.3.1 Gross Tumour Volume (GTV)

The GTV is defined as the contrast enhancing lesion on CE-T1 MRI sequence for both treatment groups. GTV can be expanded using the other clinically acquired MRI sequences according to the expertise of the local radiation oncologist and the medical team.

##### 1.3.2 Clinical Target Volume (CTV)

The CTV of both, the experimental arm and the standard arm, is defined as the GTV with addition of a 3-dimensional margin of 5 mm limited by anatomic borders. The stereotactic CTVboost of the experimental arm is equivalent to the GTV. CTV can be expanded using the other clinically acquired MRI sequences according to the expertise of the local radiation oncologist and the medical team.

##### 1.3.3 Planning Target Volume (PTV)

The PTV and PTVboost are defined as the CTV and stereotactic CTVboost plus an isotropic 2 or 3 mm margin depending on radiotherapy center, to account for day to day setup variation related to the ability to immobilize the participant. The PTV should not extend outside the body contour.

##### 1.3.4 Organs at Risk (OAR)

OAR include the following normal tissue volumes: the lenses, optic nerves and chiasm and the eyeball (includes anterior and posterior chambers); brainstem; pituitary; cochlea; skin (a 3 mm thick rim) and the uninvolved brain (= brain – CTV). OARs will be delineated following the local guidelines of the participating centers and will typically follow atlases such as CT-based OAR atlas [46] or the European Partical Therapy Network (EPTN)-consensus based atlas [47] summarized in Table A1. The complete atlas is provided as supplemental material

of the published article, available at <https://ars.els-cdn.com/content/image/1-s2.0-S0167814015004016-mmc1.pdf> .

Table A1. Definition of OARs summarized from the head and neck OAR guideline (DAHANCA, EORTC, GORTEC, HKNPCSG, NCIC CTG, NCRI, NRG Oncology and TROG consensus guidelines) [46].

| Organ           | Definition                                                                                                                                                                                                                                                                                                                                                                                                                                                                                                                                                            |
|-----------------|-----------------------------------------------------------------------------------------------------------------------------------------------------------------------------------------------------------------------------------------------------------------------------------------------------------------------------------------------------------------------------------------------------------------------------------------------------------------------------------------------------------------------------------------------------------------------|
| Eyeball         | The anterior and posterior segment of the eyeball are combined.
The anterior segment of the eyeball consists of the structures ventral from the vitreous humor, including the cornea, iris, ciliary body, and lens.
The posterior segment of the eyeball is located posteriorly to the lens, and consists of the anterior hyaloid membrane and all of the posterior optical structures including the vitreous humor, retina, and choroid. The optic nerve is excluded from this contour. The entire retina is included in the posterior segment of the eyeball. |
| Cochlea         | The cochlea is embedded in the temporal bone, located lateral to the internal auditory meatus, which can best be recognized in CT bone view settings                                                                                                                                                                                                                                                                                                                                                                                                                  |
| Brainstem       | The cranial border of the brainstem is defined as the slice where the optic chiasm is visible, the caudal border as the tip of the dens of C2 (cranial border of the spinal cord). MRI is recommended for delineation of the brainstem.                                                                                                                                                                                                                                                                                                                               |
| Pituitary gland | The pituitary gland is a very small OAR, which in general cannot be identified easily on CT. Alternatively, therefore, the inner part of the sella turcica will be used as surrogate anatomical bony structure.
The borders of the pituitary gland can be defined best in the sagittal view.                                                                                                                                                                                                                                                                       |
| Optic chiasm    | The optic chiasm is located in the subarachnoid space of the suprasellar cistern. Typically, it is located 1 cm superior to the pituitary gland, located in the sella turcica. MRI is recommended for delineation of the optic chiasm, 5mm of optic nerve and tract is incorporated in the chiasm, forming an X.                                                                                                                                                                                                                                                      |
| Optic nerve     | The optic nerve is usually 2–5 mm thick and in general is clearly identifiable on CT. It has to be contoured all the way from the posterior edge of the eyeball, through the bony optic canal to the optic chiasm. MRI is recommended for a better delineation of the optic nerve, at least close to the optic chiasm.                                                                                                                                                                                                                                                |
| Brain           | The delineation of the brain includes brain vessels, and excludes the brainstem. CT bone settings are recommended.                                                                                                                                                                                                                                                                                                                                                                                                                                                    |

[figure not shown]

Figure A1. Delineation of the cochlea in CT bone settings (purple).

[figure not shown]

Figure A2. Delineation of the optic nerves (pink and green).

[figure not shown]

Figure A3. Delineation of the eyeballs (green, white) and lenses (white).

[figure not shown]

Figure A4. Delineation of the pituitary gland (yellow) in CT bone setting.

[figure not shown]

Figure A5. Delineation of the optic chiasm (brown) and brainstem (green).

### 1.3.5 Recovery potential

With regard to the recovery potential in the brain after prior irradiation, the following schedule will be utilized[48]:

- No recovery within 1 year.
- 30% recovery after 1 year.
- 50% recovery after 2 years.

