### 4.3 Exclusion criteria

A potential subject who meets any of the following criteria will be excluded from participation in this study (arm 1 and 2):

- Previous re-irradiation or prior radiosurgery or prior treatment with interstitial radioactive seeds.
- CE-T1 tumor diameter greater than 6cm ( reflecting a spherical tumor of 125cc).
- Time interval of less than 6 months after prior radiotherapy.
- Time interval of less than 3 weeks after last re-resection (1 week for biopsy).
- Known carcinoma < 3 years ago (excluding Carcinoma in situ of the cervix, basal cell carcinoma, squamous cell carcinoma of the skin) requiring immediate treatment interfering with study therapy.
- Women with childbearing potential without adequate contraception.

If a patient is not eligible for arm 1 based on the MRI results (e.g. T1-CE diameter >6 cm, reflecting a spherical tumor of 125 cc), these non-eligible patients are being replaced by new patients. These non-eligible patients are not included in the statistical analysis of the trial and treated with the physicians' choice.

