### 1.6 Dose Limitation to Organs at Risk

It is important to minimize the dose to the OARs whenever possible. This must be weighed against the possibility of sub-optimal treatment of the target volume.

**Table A1. Dose constraints for OARs in Gy. Radiobiological calculations performed with  $\alpha/\beta = 2$  Gy. To calculate the dose constraint at ReRT, the initial dose should be subtracted from the cumulative dose constraint for OARs. Subsequently, the ReRT EQD2 should be converted to the dose constraint for the OARs according to the treatment arm. The ReRT dose of OARs should never exceed the EQD2 and total dose constraint given for initial treatment (shown in column 'Constraint at ReRT').**

*Example:* Optic Chiasm ReRT dose = 9.8Gy ( $\leq 38$ ) in 10 fractions = 7Gy EQD2 ( $\leq 54$ ). Initial dose 53.2Gy in 30 fractions = 51Gy EQD2. Cumulative dose = 51 + 7 = 58Gy, is  $\leq 81$ .

| Constraint | OAR             | Constraint at ReRT (without considering previous radiation therapy)                |                                                              | Cumulative constraint
(Initial RT + ReRT)                  |
|------------|-----------------|------------------------------------------------------------------------------------|--------------------------------------------------------------|---------------------------------------------------------------|
|            |                 | Total D max 0.1cc dose (unless otherwise specified) at $\alpha/\beta=2$ |                                                              |                                                               |
|            |                 | EQD2                                                                               | Total physical dose at
4 x 7.5 Gy and 4 x 5.5 Gy          | EQD2                                                          |
| Hard       | Optic nerves    | $\leq 60$ Gy                                                                       | $\leq 27$ Gy                                                 | $\leq 90$ Gy                                                  |
|            | Optic chiasm    | $\leq 60$ Gy                                                                       | $\leq 27$ Gy                                                 | $\leq 90$ Gy                                                  |

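### Appendix 1.3.5 announces a brain recovery schedule that no dose-limit calculation uses, and the worked example in Appendix 1.6 does not match its own table

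*Protocol*

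**What the plan says.** Appendix 1.3.5 opens with "With regard to the recovery potential in the brain after prior irradiation, the following schedule will be utilized". The schedule has three steps: "No recovery within 1 year", "30% recovery after 1 year" and "50% recovery after 2 years".

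Appendix 1.6 gives the operating rule for organs at risk: "To calculate the dose constraint at ReRT, the initial dose should be subtracted from the cumulative dose constraint for OARs". The re-irradiation dose is also capped at the single-course limit. The table has one cumulative column, with no interval term and no reference to 1.3.5. Its rows are optic nerves, chiasm, brain stem, eyeballs, lenses, pituitary and cochlea. Appendix 1.3.4 also lists uninvolved brain as an organ at risk, but the table has no row for it.

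The example printed with the table concerns the optic chiasm. It starts from "Initial dose 53.2Gy in 30 fractions = 51Gy EQD2", adds 7 Gy EQD2 from 10 fractions, and compares the total of 58 Gy with 81 Gy.

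On the interval, section 4.3 excludes only "Time interval of less than 6 months after prior radiotherapy". Patients at 6 to 12 months, 1 to 2 years and beyond 2 years can therefore all enter.

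**The concern.** The schedule is worded as something that will be used, but a planner who follows Appendix 1.6 never meets it. The only interval-dependent statement about tolerance is therefore detached from the only procedure for setting limits. The example, which should settle how the procedure works, uses a fraction number and chiasm limits that the arm 1 table does not give.

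Radiotherapy is planned locally in each center under this appendix (section 5.1). Two centers could read it differently and plan the same patient to different limits. That bears on safety, and it would make toxicity pooled across centers harder to interpret. The sample size and the primary survival analysis are not affected.

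**Working it through.** **Inputs.** The single-course and cumulative limits, the example and α/β = 2 Gy come from Appendix 1.6. The recovery steps come from Appendix 1.3.5, and the 6-month minimum from section 4.3. For total dose D in n fractions, EQD2 = D × (D/n + 2) / 4.

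**1. The cumulative column.** Multiply each single-course EQD2 limit by 1.5:

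| Single-course (Gy) | × 1.5 | Table, cumulative (Gy) |
|---|---|---|
| 60 | 90 | 90 |
| 55 | 82.5 | 83 |
| 54 to 59 (brain stem, < 10 cc) | 81 to 88.5 | 81 to 89 |
| 45 | 67.5 | 68 |
| 6 (lens mean) | 9 | 9 |
| 10 (lens max) | 15 | 15 |

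After rounding, the factor is 1.5 throughout, whatever the interval.

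**2. Where the schedule is used.** The recovery percentages appear in 1.3.5 and in no formula, table or example. The rule in 1.6 subtracts the full initial dose, and the example adds the full 51 Gy. The dose rationale in section 5.2 also refers to a fixed cumulative dose, with no interval term.

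**3. The worked example.**
- Re-irradiation: 9.8 × (0.98 + 2) / 4 = 7.3 Gy. The stated 7 reproduces.
- Initial course: 53.2 × (53.2/30 + 2) / 4 = 53.2 × 3.773 / 4 = 50.2 Gy. The stated 51 does not reproduce; 29 fractions would give 51.0.
- Limits:

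| Chiasm limits | EQD2 at re-irradiation (Gy) | Physical dose (Gy) | Cumulative EQD2 (Gy) |
|---|---|---|---|
| Example | 54 | 38 in 10 fractions | 81 |
| Table, hard | 60 | 27 in 4 fractions | 90 |
| Table, soft | 55 | 26 in 4 fractions | 83 |

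The example's 81 is 1.5 × 54, so it follows the same factor from a chiasm limit that the table does not list. Its total of 58 Gy is below 81, 83 and 90, and its 7 Gy is below 54, 55 and 60. The pass result is unchanged when the table's chiasm limits are put in.

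**4. Illustration of what is left open.** The protocol does not say how recovery would act. Assume, for illustration only, that 1.3.5 applies to the chiasm and discounts the initial dose against the single-course limit L. The dose left for re-irradiation is then L − (1 − r) × 51, with r = 0, 0.3 or 0.5. The table leaves the cumulative limit minus 51.

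| EQD2 left (Gy) | Table, any interval | r = 0 | r = 0.3 | r = 0.5 |
|---|---|---|---|---|
| Hard (60/90) | 39 | 9 | 24.3 | 34.5 |
| Soft (55/83) | 32 | 4 | 19.3 | 29.5 |

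A second conceivable reading discounts the initial dose and also keeps the 90 Gy column. It leaves 39 Gy, then 90 − 35.7 = 54.3 Gy, then 90 − 25.5 = 64.5 Gy, where the 60 Gy single-course cap would take over. This reading would count recovery twice.

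The factor of 1.5 coincides with the 50% step only when the initial dose equals the single-course limit: 60 + 0.5 × 60 = 90. At 51 Gy the hard limit implies (90 − 60)/51 = 59% and the soft limit (83 − 55)/51 = 55%.

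**The case against.** The strongest reply is about scope. The schedule is worded for the brain, and the organ definitions in Appendix 1.3.4 delineate brain without the brainstem. The table covers other structures. On that reading 1.3.5 and 1.6 concern different tissues and do not contradict each other. Section 1.6 is also complete in itself: it has a subtraction rule, a cap and an example with no discount. This stands as far as it goes, and it rules out calling the two sections a plain contradiction. It does not rescue 1.3.5, because a brain-only schedule then has no row, limit or formula to act on.

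A reader might infer that the table allows patients treated at 6 to 24 months too much dose, by the amounts illustrated above. The documents do not support that. They never say that the 1.5 factor represents recovery, never describe the discounting used in the illustration, and never extend the brain schedule to the chiasm. Nor does the text instruct anyone to count recovery twice.

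On the example, 54 and 81 do occur in the table, but only as the lower ends of the brain-stem partial-volume ranges, not as chiasm limits. The 51 against 50.2 Gy difference is small. The mismatch in limits and fraction number remains.

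Practical impact is not shown. The protocol gives neither the share of patients with short intervals nor how often a listed organ would limit the plan. The toxicity terms named for interim monitoring in section 8.3 include central nervous system necrosis, edema and seizures, so an effect on the stopping boundaries is not demonstrated.

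**Conclusion.** The point holds as two inconsistencies in the appendix.

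First, a schedule that the protocol says will be used enters no calculation. If it is meant for the listed organs, it conflicts with the fixed cumulative column, most clearly for intervals under 2 years. If it is meant for brain only, it is applied nowhere. The text does not decide between the two.

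Second, the worked example tests the chiasm against limits and a fraction number that differ from the table's chiasm rows, and one of its conversions is off by 0.8 Gy. This needs no assumption beyond the stated α/β.

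The size of the first inconsistency cannot be fixed from the document. The example's initial dose and the hard limit give 39 Gy EQD2 under the table, against 9 to 34.5 Gy under one assumed way of applying recovery. These figures show how much the missing statement could matter. They are not an estimate of excess dose. The point should be corrected because centers rely on these limits for safety, and it carries no view on which limit or recovery rule is right.

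**What to change.** The sponsor should reconcile Appendix 1.3.5, the cumulative column in 1.6 and the worked example. The revised text should state once which structures the schedule governs, and whether and how the interval since prior radiotherapy enters the limits. If the schedule is for brain only, the text should say where it is used. The example should be redone with the table's own chiasm limits, the arm 1 fraction number and a corrected EQD2 for the initial course. Any figure for remaining dose by interval should be marked as illustrative unless the method is specified. Which limit or recovery rule applies is for the responsible clinicians and physicists to decide.

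The cost is a correction to the appendix and a notice to the participating centers. No statistical design element changes.
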